## Methods

### Study Design

The trial is a 24-month, multicenter, pragmatic, open-label, 2-arm, parallel-group, individually randomized group treatment trial assessing the clinical and cost effectiveness of the HEAL-D program compared with standard DSMES programs in Black African and Black Caribbean adults living with T2D. A total of 300 Black African and Black Caribbean adults living with T2D will be recruited and randomly allocated to either the HEAL-D program (n=150) or a standard DSMES program (control, n=150). Outcome assessments will be conducted at baseline and 6, 12, and 24 months after randomization (Figure 1). Embedded within the trial are an internal feasibility assessment of recruitment, allocation and intervention engagement; a health economic analysis; a mixed methods process evaluation of intervention delivery, fidelity, implementation and acceptability; and study within a project (SWAP) to assess the impact of MLTC on the uptake of and engagement with HEAL-D, and the impact of the intervention on MLTC.

The trial is funded by the National Institute for Health Research (NIHR) Health Technology Assessment Program (NIHR151372) and is registered with ISRCTN (14344948), which adheres to the World Health Organization (WHO) Trial Registration Dataset. Health Research Authority and Research Ethics Council approval was received on April 22, 2024.

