### Data Collection Procedures

As depicted in Figure 1, data will be collected prerandomization (baseline), 6 months, 12 months (primary endpoint), and 24 months post randomization. The primary outcome, secondary and exploratory outcomes, along with their associated timepoints of administration, are listed in Table 1. The measures will be collected during an in-person assessment of approximately 2 hours duration at an NHS research or primary care clinic facility. It is intended that all measures be completed on a single day, but they may occur across a maximum 14-day window. This might include completion of questionnaires via telephone or video call, or primary care or home visits for anthropometric or questionnaire measures. All staff will be trained in best practices for data collection and management by the trial manager, who also monitors data quality. Outcome assessors of the primary outcome (HbA_1c_) and other blood measurements will be blinded to treatment allocation; however, it is not possible to ensure blinding of assessors for the other outcome measures. Trial data will be recorded on a centralized web-based data collection platform (REDCap).

Multiple strategies will be implemented to maximize participant retention and completion of outcome assessments, including offering outcome assessments at different times of the day, remuneration for completion of outcome assessments (£50 [US $68] per assessment visit plus travel costs; there is no remuneration for participation in treatment sessions). Participants will be encouraged to complete outcome assessments, even if they did not attend treatment sessions or missed a previous outcome assessment. Participants will also receive brief study review contacts (via telephone or video calls) from the research team at three monthly intervals where assessment visits are not scheduled, to review ongoing willingness to continue.

**Table 1 table1:** Study measures and assessment timepoints.

Outcome measure			Timepoint			
			Baseline	6 months	12 months	24 months

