### Secondary and Exploratory Outcomes

At 6 and 24 months, HbA_1c_ will be measured as a secondary outcome to allow exploration of the time-course of any observed changes and impact of HEAL-D over a longer period. Other secondary outcomes (Table 1), measured at 6, 12, and 24 months, are grouped into holistic health domains and include cardiovascular risk factors, psychological well-being and self-management support, lifestyle behaviors, and health economics.

Tertiary outcomes are low-density lipoprotein-cholesterol, triglycerides, body fat percentage, changes to glucose-lowering and antihypertensive therapies (including addition, removal, or dose adjustment), and changes in MLTC status (including additional diagnoses, remission, or changes in severity).

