### Statistical Analysis

Primary analysis of change in HbA_1c_ at 12 months will be conducted using a mixed effects model with a random effect for the group attended; individuals in the control arm will be treated as groups of size 1 [64]. Treatment arm, center, and baseline HbA_1c_ will be included as fixed effects. The primary analysis will be repeated to include an interaction term between treatment and mode of delivery (F2F or remote) to explore any differential treatment effect among groups. The presence of an interaction will be tested using a likelihood ratio test. The prespecified subgroup analyses of the primary outcome will assess whether the effectiveness of the intervention is dependent on baseline HbA_1c_ or center. This will be assessed by adding interaction terms between group allocation and the potential effect modifiers to the linear regression, one at a time. The analysis exploring the change in treatment effect over time for the secondary outcomes will follow the methodology of the primary analysis, with an additional random effect for the individual to account for within-individual correlation over time, a fixed effect for time, and an interaction between treatment and time effect. Mediation analysis will be conducted using multilevel structural equation modeling [65]. To account for missing data, multiple imputation will be undertaken, provided we have strong predictors of missingness and an appropriate imputation model. Diagnostic checks will be performed to assess this. The missing data mechanism will be assumed to be missing at random. Individual analyses on each imputed dataset will be combined using the Rubin rules. Sensitivity analyses will be conducted to assess the robustness of the primary conclusions to the imputation strategy used.

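### A single random effect per person in the over-time analysis assumes equal variance and equal correlation across unequally spaced visits; if correlation fades, the 24-versus-6-month contrast gets too small a standard error

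*Protocol article*

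**What the plan says.** The Statistical Analysis section of the protocol article defines the primary model as a "mixed effects model with a random effect for the group attended; individuals in the control arm will be treated as groups of size 1". It adds: "Treatment arm, center, and baseline HbA_1c_ will be included as fixed effects". For the later analysis it states: "The analysis exploring the change in treatment effect over time for the secondary outcomes will follow the methodology of the primary analysis". To that it adds one element for the person, "with an additional random effect for the individual to account for within-individual correlation over time, a fixed effect for time". A treatment-by-time interaction completes the model. It names no random slope, residual covariance structure, visit-specific variance or robust standard error.

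The Study Design section sets the schedule: "Outcome assessments will be conducted at baseline and 6, 12, and 24 months after randomization". The Secondary and Exploratory Outcomes section says that HbA1c is measured at 6 and 24 months "to allow exploration of the time-course of any observed changes and impact of HEAL-D over a longer period".

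**The concern.** The random effect for the individual is the stated device for within-person correlation. With the usual independent, equal-variance residuals it gives compound symmetry: the same variance at 6, 12 and 24 months, and the same correlation for every pair of visits. The pairs are 6, 12 and 18 months apart. According to the Intervention Group section, the HEAL-D sessions run over about 6 months, so the first follow-up falls near the end of the programme and the later ones come after it. Equal correlation across these gaps is a special case.

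The analysis is meant to show how the treatment effect changes over time. The standard error of a difference between two visits depends directly on the correlation assumed for that pair. If the single correlation is too high for the 6-24 pair and too low for the 6-12 pair, the two contrasts err in opposite directions. At stake is how firmly the report can say that an effect seen at 6 months is maintained or lost by 24 months.

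**Working it through.** The plan gives no figure on this point to reproduce, and no between-visit correlation. The correlations below are assumptions. The visit times come from the Study Design section, and the SD of 11 mmol/mol and the 5% two-sided level from the Sample Size Calculation. With equal SDs the SD cancels.

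**Formulas (complete data).** Let V be the true 3 x 3 covariance over 6, 12 and 24 months. Compound symmetry fits v = the mean of the diagonal and c = the mean of the off-diagonal elements.
- Contrast between visits j and k: model SE / true SE = sqrt[2(v - c) / (V_jj + V_kk - 2V_jk)].
- Effect at visit k: model SE / true SE = sqrt(v / V_kk).
- True two-sided error rate = 2[1 - Φ(1.96 x ratio)].

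**Worked case.** Take correlations 0.70 (6-12), 0.60 (12-24), 0.45 (6-24) and equal SDs. The mean correlation is (0.70 + 0.60 + 0.45)/3 = 0.5833.
- 24 versus 6: sqrt[(1 - 0.5833)/(1 - 0.45)] = sqrt(0.4167/0.55) = 0.870. Error rate 2[1 - Φ(1.706)] = 8.8%.
- 12 versus 6: sqrt(0.4167/0.30) = 1.179. Error rate 2[1 - Φ(2.310)] = 2.1%.

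**Range (equal SDs).**

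| Assumed 6-12 / 12-24 / 6-24 | 24 vs 6: ratio, error | 12 vs 6: ratio, error | Joint 2-df test |
|---|---|---|---|
| 0.60 / 0.60 / 0.60 | 1.000, 5.0% | 1.000, 5.0% | 5.0% |
| 0.65 / 0.60 / 0.55 | 0.943, 6.5% | 1.069, 3.6% | 5.1% |
| 0.60 / 0.50 / 0.40 | 0.913, 7.4% | 1.118, 2.8% | 5.2% |
| 0.70 / 0.60 / 0.45 | 0.870, 8.8% | 1.179, 2.1% | 5.4% |

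The last column is simulated. A steeper pattern, 0.8 per 6 months (0.80/0.64/0.512), gives 0.846 and 9.7% for 24 versus 6.

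**The 24-month effect.** With equal SDs, sqrt(v/V_kk) = 1 whatever the correlations, so complete data show no error. If the SD grows 10, 11, 12.5 mmol/mol (assumed), v = (100 + 121 + 156.25)/3 = 125.75 and the ratio is sqrt(125.75/156.25) = 0.897. The SE is then 10% too small and the error rate 7.9%. If the SD falls 12, 11, 10, v = 121.67 and the ratio is sqrt(121.67/100) = 1.103, so the SE is too large.

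**With loss to follow-up.** This check used 150 per arm and cumulative loss of 7%, 15% and 22% at the three visits. The first two figures stand in the Sample Size Calculation; the 22% is assumed. Group clustering was left out because the planned intracluster correlation is 0.01. The compound-symmetry SE was compared with the sandwich SE.
- For correlations from 0.70/0.65/0.60 to 0.80/0.64/0.512, true/model SE was 1.07 to 1.19 for the 6-to-24-month change and 1.005 to 1.015 for the 24-month effect.
- Residual variance can grow even with a constant raw SD, because baseline enters with one common slope. With visit correlations of 0.75/0.65/0.55, a baseline correlation fading 0.65/0.60/0.55 gave 1.06 for the 24-month effect, and 0.7/0.6/0.5 gave 1.11.

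**The case against.** Four points on the other side carry weight.

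**The text does not say that there is only a random intercept.** It does not state independent or equal-variance residuals either. Residual structure is ordinary SAP content, and the SAP is not shown. This stands as a caution: the SAP may already add a structure. It does not dispose of the point, because the article names the device meant to carry the within-person correlation, and its plain reading is compound symmetry.

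**The 24-versus-6-month contrast is not named as a test.** The plan specifies a treatment-by-time interaction. With time as a factor, its direct test has two degrees of freedom and stays near 5% in the table. This also stands. The error rates of 6.5% to 8.8% apply when the maintenance question is answered by comparing the two visits, which the stated interest in the time course invites.

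**The correlations are assumed.** Equal correlation gives no error at all, so the size is conditional.

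**The analysis is exploratory and secondary.** The 12-month primary model uses one follow-up visit and is not involved.

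A reader might infer two stronger claims. One is that the 24-month effect probably has too narrow an interval. Unequal correlation alone moves its SE by about 1%, and the documents do not say whether variance rises or falls. The other is that dropout combined with a wrong covariance biases the 24-month estimates. That bias has not been quantified, and the plan provides for multiple imputation under missing at random, conditional on diagnostic checks, with sensitivity analyses. Where imputation is used, the imputation model also carries the between-visit associations.

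**Conclusion.** The point holds in limited form. The specification, read ordinarily, imposes one variance and one correlation on visits with unequal gaps. If correlation fades within the assumed range, the SE of the 24-versus-6-month change in treatment effect is 6% to 13% too small and the 12-versus-6-month SE is 7% to 18% too large. The 24-month effect may be too narrow by about 10% if residual variance grows roughly as assumed, and too wide if it falls. These sizes rest on assumed correlations and SDs. The joint interaction test and the primary conclusion are not threatened. The matter is worth correcting because it touches the question that the longitudinal analysis is meant to answer, and correcting it is inexpensive.

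**What to change.** In the SAP, for continuous outcomes measured at 6, 12 and 24 months:
- fit visit as a three-level factor with treatment by visit;
- replace the individual random effect with an unstructured covariance across the three visits;
- keep the random effect for the HEAL-D group;
- report the treatment effect at each visit and the 24-versus-6-month contrast.

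State in advance that, if this does not converge for an outcome, a simpler heterogeneous structure or robust standard errors will be used. Categorical outcomes, such as the low/moderate/high activity classification, may keep the individual random effect. Accelerometry, taken only at baseline and 12 months, needs no longitudinal covariance.

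The cost is SAP wording, four extra covariance parameters (six instead of two) and occasional use of the fallback. About 255 people are expected at 12 months (300 x 0.85). Fewer may remain at 24 months, but that is still ample for six parameters. If correlations and variances really are equal, almost nothing is lost. The article places the last visit in June 2027 and the start of analysis in July 2027, so the change can be fixed before the 24-month data are complete.

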### Safety Reporting

As the trial is not a clinical trial of an investigational medicinal product, monitoring of pharmacovigilance is not relevant. Adverse events will be recorded and discussed periodically with the TSC as required. Any safety concerns that arise as a result will be reported to the sponsor as soon as possible. Serious adverse events (SAEs) will be reported to the sponsor within 24 hours of becoming aware of the event. The principal investigator or another delegated physician (as agreed by the sponsor) will be responsible for the review and sign-off of the SAE and the assessment of causality (ie, whether an event is related to a study procedure or intervention). Events will be followed up on until the event has been resolved or a final outcome has been reached. In addition to the expedited reporting above, the chief investigator (CI) shall submit, once a year throughout the study or on request, an Annual Report to the Ethics Committee, which lists all SAEs.

### Posttrial Care

Provisions will be put in place for posttrial access for all participants who still need an intervention identified as individually beneficial in the trial. This includes referral to local providers of physical activity services and psychosocial support (ie, primary care services).

### Ethical Considerations

The trial has been approved by the Health Research Authority (IRAS ID: 326064) and East Midlands—Leicester South Research Ethics Committee (REC reference: 24/EM/0079). The trial will be conducted in full conformity with the current revision of the Declaration of Helsinki (last amended October 2000, with additional footnotes added 2002 and 2004), the UK Policy Framework for Health and Social Care Research (2017), and International Council for Harmonization of Technical Requirements for Pharmaceuticals for Human Use Good Clinical Practice relevant regulations. Potential participants who express an interest in participating in the trial will be provided with an information video or leaflet providing full details of the trial and what is entailed. Participants will be given an opportunity to discuss participation with a trial coordinator. Those who decide to participate will be required to provide written informed consent prior to the collection of research data; consent will be collected by trained research staff at the baseline assessment visit. Participant data will be pseudonymized and treated in confidence and in compliance with the International Council for Harmonization of Technical Requirements for Pharmaceuticals for Human Use Good Clinical Practice, the UK Policy Framework for Health and Social Care, and the UK General Data Protection Regulation. All investigators and trial site staff will comply with the requirements of the Data Protection Act or General Data Protection Regulation with regard to the collection, storage, processing, and disclosure of personal information and will uphold the Act’s core principles. The CI will have access to the trial documentation and will be the data custodian. Participants will receive £50 (US $68) for each of the assessment visits they attend in compensation for their time commitment and will have their travel costs reimbursed. Individuals who participate in an interview for the process evaluation will receive £20 (US $27) to compensate for their time. Participants will not receive financial reimbursement for attending their allocated treatment.

### Study Oversight and Monitoring

This trial is sponsored by The University of Leicester, United Kingdom (reference: 0928). The University of Leicester operates a risk-based monitoring and audit program, to which this study will be subject. The Pragmatic Clinical Trials Unit, Queen Mary University of London, United Kingdom, will provide support regarding data management, statistical analysis, and quality assurance. A TSC, consisting of an independent statistician, health economist, person of Black African and Black Caribbean ethnicity with lived experience of T2D, and other independent subject specialists, has been formed and will offer independent strategic oversight throughout the trial. In line with the European Medicines Agency Guideline on data monitoring committees [69], the sponsor determined that a Data Monitoring and Ethics Committee is not required for the trial.

### Protocol Amendments

Amendments will be submitted to the sponsor in the first instance for review and approval. The CI, in agreement with the sponsor, will then submit information to the appropriate body (HRA or REC) for approval. Any amendments will also be approved by the trial funder and communicated to the trial registry.

## Results

The trial, funded by the NIHR, will run for 48 months in total (August 1, 2023, to July 31, 2027). Site “green light” was received on August 15, 2024, for London; November 29, 2024, for Manchester; and January 31, 2025, in the West Midlands. Recruitment commenced in August 2024 and is due to run over 11 months. As of March 26, 2025, a total of 76 participants have consented, and 72 participants have been randomized. The “last patient, last visit” is expected in June 2027; primary data analysis is expected to begin in July 2027. Final results are anticipated to be available in September 2027, and publication is expected by the end of 2027.

## Discussion

### Overview

The HEAL-D trial will evaluate if a culturally tailored DSMES program, provided in person or remotely, via videoconferencing, is clinically and cost-effective, in comparison with standard DSMES programs, at improving glycemic control (HbA_1c_) at 12-month follow-up in adults of Black African and Black Caribbean ethnicity living with T2D. It is hypothesized that the provision of a DSMES program that is sensitive to the cultural health beliefs and practices of adults of African and Caribbean heritage will promote clinically meaningful improvements in T2D self-management.

### Principal Findings

Principally, the trial is designed to evaluate the effectiveness of the HEAL-D intervention, compared to standard DSMES programs, on glycemic control at 12 months. In addition, a range of important clinical and patient-reported outcome measures, including cardiovascular risk factors, psychological well-being and QoL, T2D knowledge and self-efficacy, and diet and physical activity behaviors, will be collected at 6, 12, and 24 months. Importantly, the 24-month endpoint will enable assessment of the longer-term impact of the intervention on the clinical and patient-reported outcomes.

### Comparison to Prior Work

To date, in the United Kingdom, there have been no trial evaluations of culturally tailored DSMES programs for T2D self-management in adults of Black African and Black Caribbean ethnicity [29,70]. However, previous trials in the United States have demonstrated significant reductions in HbA_1c_, as well as improvements in T2D knowledge, which were associated with HbA_1c_ improvements [29].

### Strengths and Limitations

The HEAL-D trial builds on a large program of co-design research, which engaged a wide range of stakeholders (people of Black African and Black Caribbean ethnicity living with T2D, healthcare practitioners and commissioners, and community leaders) in the development of the intervention to ensure its relevance to both patients and healthcare service providers [29-33]. Furthermore, the acceptability of the HEAL-D intervention has been rigorously evaluated, and the feasibility of conducting a randomized controlled trial was assessed in earlier work [34,41-43,71,72]; the design of this trial has been informed by those evaluations, reflecting the main findings. People with lived experience of T2D continue to inform the delivery of the trial, as well as future dissemination, through involvement in the trial PPIE stakeholder group.

### Future Directions

A key concern in clinical practice is the accessibility of educational programs for the population in question. The development of both F2F and remote delivery formats hopefully maximizes the potential for pragmatic use in healthcare, whilst the availability of digital delivery may be particularly beneficial for ethnic minority groups [23]. For example, remote programs can reach those who are unable to attend F2F sessions [73] and can bring together individuals from areas with low population densities of a given ethnic group [23]. Digital interventions may also be more cost-effective, as spotlighted during the COVID-19 pandemic [74]. Furthermore, ongoing PPIE during the development of the HEAL-D intervention has enabled the production of a program and related materials that patients have found both engaging and accessible, as described previously [30-32]. By incorporating assessments of effectiveness, cost-effectiveness, a thorough process evaluation, and SWAP into the trial design, it is ensured that the needs of all stakeholders continue to be accounted for, thus promoting the feasibility of implementing the HEAL-D program within healthcare services.

